#### Training of PASS clinicians and the community health partner

The PASS clinicians generally are licensed behavioral health professionals embedded in the practices. Advanced trainees (e.g., post-doctoral fellows in psychology) receiving in-session supervision by an attending provider or additional licensed professionals are enlisted as needed to ensure enrolled families assigned to the PASS condition receive the intervention in a timely way. Each clinician will receive 4–6 h of training from a trained, experienced PASS clinician, prior to intervention. PASS clinicians will be trained to implement the treatment manual and attend to process variables, including establishing trust, listening actively, and re-directing tangential comments. In addition, a senior PASS clinician will provide 4 h of training and bi-weekly consultation with the Community Health Partner. Community Health Partner training will include an overview of the PASS intervention as well as training specific to the role of the Community Health Partner.

#### Assessment of intervention fidelity

PASS sessions will be audio recorded to enable our team to examine intervention content fidelity. The PASS treatment manual includes two standard sessions (sessions one and two) that are always presented and a variable number of additional sessions (sessions 3 +) that can be selected depending on presenting concern and family need or preference. Checklists reflecting session components will be used to assess content fidelity. Up to four sessions will be selected for content coding for each participant in the PASS condition. Sessions one and two will always be coded. One randomly selected session from sessions 3–5 and another from sessions 6 + will be selected for coding. Independent coders who have previous training in psychosocial treatment of ADHD will code all selected tapes and 25% of tapes will be double-coded to establish inter-rater reliability. An intraclass correlation coefficient (ICC) of at least 0.6 will indicate acceptable agreement [37].

The Community Health Partner will complete a survey after each encounter with a caregiver that provides information on topics discussed, barriers, stressors, strategies to address barriers and stressors, caregiver perceptions of care, resources, and the support process included in the call. To monitor Community Health Partner process fidelity, we will use a self-evaluation checklist completed by Community Health Partners after contact with a family. Process items include establishing trust, listening attentively, and re-directing tangential comments [38].

#### Measures of outcomes – examined for objective 1

Outcomes are differentiated into primary versus secondary and informant providing data (parent, teacher, child self-report). Two parent-report measures (ratings of homework performance and behavior compliance) have been identified as primary because these are a major focus of the PASS intervention. Teacher-report measures are secondary because of challenges obtaining these data due in large part to the burden placed on schools. Child self-report measures are secondary because some children, especially those under the age of 8, may have difficulty understanding and responding to these measures.

#### Primary outcomes

The Inattention/Task Avoidance factor of the *Homework Problem Checklist* (HPC) [39] will be used as a parent-report measure of child academic performance. This 12-item scale has strong psychometric properties [40] and is responsive to family-school intervention programs [41, 42]. Behavior compliance will be determined by assessing the severity of child disruptive behavior using the eight items pertaining to oppositional-defiant disorder from the *Vanderbilt Assessment Scale* parent version. The psychometric properties of parent and teacher reports on this measure have been shown to be adequate [43, 44].

#### Parenting practices

The *Parent–Child Relationship Questionnaire* (PCRQ) [51] will assess parent perceptions of their parenting practices. The Negative/Ineffective Discipline factor and four items from the Positive Involvement factor will be administered. This measure has been shown to be internally consistent and sensitive to the effects of behavioral intervention [41, 52].

#### Family empowerment

Parent empowerment regarding their knowledge of how to obtain services for their children will be assessed using the Service System factor of the *Family Empowerment Scale*. This twelve-item scale has been shown to have adequate reliability (alpha = 0.87; test–retest = 0.77) and validity [53].

#### Team-based care

To evaluate parental perceptions of team-based care, a seven-item scale was derived from the Clinician and Group Survey, Version 3.0 of the *Consumer Assessment of Healthcare Providers and Systems* (CAHPS, https://cahps.ahrq.gov/surveys-guidance/cg/about/index.html). The scale includes four Communication and four Care Coordination items. The psychometric properties of this scale will be examined during the study.

#### Parent-teacher involvement

The Quality of Parent-Teacher Relationship subscale of the *Parent-Teacher Involvement Questionnaire* (PTIQ) [54] will be used to evaluate the quality of the family-school relationship. The parent version of the form includes 6 items, and the teacher version consists of 5 items. Subscales have been validated in families of youth with ADHD and have demonstrated acceptable internal consistency and validity [55].

### Measures of variables for subgroup analyses (Assessed at baseline; examined for objective 4)

#### Sociodemographic factors

Parents will be asked to classify their and their *child’s race and ethnicity* and report the *primary caregiver’s highest educational attainment* at the current time. To assess *household income and poverty level*, items will be derived from the National Health Interview Survey (NHIS) Family Questionnaire (2007) that assess household income of all family members from all sources before taxes in the prior calendar year and whether the family is above or below the poverty level.

To measure *financial resource strain*, a single item from the Study of Women’s Health Across the Nation (SWAN) study will be administered to assess family ability to pay for basics such as food and housing. Prior research supports the item’s validity [56].

To assess *caregiver perceived stress,* caregivers will complete the *Perceived Stress Scale* (PSS), a 10-item measure of the degree to which respondents feel that their lives are unpredictable and overloaded in the past month. The PSS has adequate reliability and expected associations with life stressors, depression, anxiety, and somatic symptoms [57].

To examine the health literacy of caregivers, the *Short Assessment of Health Literacy* will be used [58]. This 18-item measure was developed and validated using item response theory. The internal consistency of the scale is in the acceptable range and relatively high for caregivers with lower levels of health literacy. Correlations with other measures of health literacy are relatively high, supporting the validity of the measure.

#### Medication status

We will track medication status by: (a) asking parents to report on medication status at each data collection period using the service use form, and (b) obtaining data from the EHR related to medication prescriptions and reconciliation of active medication orders. Medication status for purposes of randomization and analysis of subgroups will be determined by parent report of medication use at baseline. In addition, we will examine whether changes in medication status (based on parent report at each data collection period) during the intervention and follow-up periods (e.g., change from off to on medication) has an effect on treatment outcomes. We will use medication data obtained from the EHR to assess for gaps in medication use for patients who are on medication at the start and end of the study period.

#### Clinical characteristics

Our team will explore whether clinical characteristics of the child at baseline, such as severity of ADHD, oppositional defiant disorder (ODD), and anxiety/depression symptoms assessed using the Vanderbilt scales, have a moderating influence on the effect of intervention on child outcomes.

### Assessment of family and provider engagement in intervention

Family attendance at sessions is documented in the electronic health record. The Community Health Partner will maintain records of all contacts (phone, email, text) initiated and successfully completed with families. Parent satisfaction with PASS will be assessed using a modified version of the Treatment Evaluation Inventory [59]. Primary care provider satisfaction with PASS will be evaluated using a measure of satisfaction developed in collaboration with clinician partners and advisors. Parent/legal guardian/caregiver satisfaction with the modality of PASS delivery (i.e., in-person or telehealth) will be assessed using a novel Acceptability of PASS Delivery Modality measure adapted for the current study from the Acceptability of Intervention Measure. The Acceptability of Intervention Measure has demonstrated strong psychometric properties and is designed to be adaptable for a wide range of populations and interventions [60].

### Participant timeline

Study involvement for participants will begin at the time of family consent. The study will end for participants at the time of follow-up data collection. See Table 2 for a study timeline.

**Table 2. Tab2:**
[figure not shown]
Timeline and Measure Completion

*PASS *Partnering to Achieve School Success, *TAU *Treatment as usual, *HPC *Homework Problem Checklist, Inattention/Task Avoidance subscale, *APS *Academic Proficiency Scale, *NICHQ *National Institute for Children’s Healthcare Quality, *PROMIS *Patient-Reported Outcomes Measurement Information System, *FES *Family Empowerment Scale, *CAHPS *Consumer Assessment of Healthcare Providers and Systems, Communication and Care Coordination subscales, *PCRQ *Parent-Child Relationship Questionnaire, *PTIQ *Parent-Teacher Involvement Questionnaire, *PSS *Perceived Stress Scale, *EHR *Electronic health record, *SAHL *Short Assessment of Health Literacy, *TEI-SF *Treatment Evaluation Inventory, Short Form, *P *Parent, *C *Child, *T *Teacher, *PCP *Primary Care Provider, *CT *Clinical team, *R *Research Team.

^*^Administered at screening visit prior to enrollment.

^**^Only parent-rated Oppositional Defiant Disorder Symptoms will be administered at mid-treatment

^***^Only ODD and ADHD Symptoms will be administered at post-treatment & follow-up (both parent and teacher)

^****^Measure is only administered for PASS condition

### Sample size

Based on prior research [26, 28, 35], the magnitude of the effect size reflecting the degree of change in response to PASS vs TAU for service use and child outcomes (Objective 1) and care processes (Objective 2) is expected to be the 0.35 to 0.60 SD range. Based on prior research using a similar behavioral intervention [41], we assumed a standard deviation for a single observation = 0.50 and an autocorrelation = 0.3. Projecting an enrollment of 300 participants (150 per condition), and given an expected 20% attrition rate, we expect 240 participants will provide parent-report and child self-report data at baseline and at least one other data collection point. Using statistical methods described below, analytic models will achieve 85% power to detect an effect size as small as 0.30 SD. Given the challenges of collecting data from teachers related to the COVID-19 pandemic, the number of evaluable cases will be well below 240 (estimated to be 100). As such, analyses of teacher-report data will be exploratory. In addition, analyses of mediation (Objective 3) and subgroup effects (Objective 4) will be exploratory.

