### Assignment of interventions

Participants will be randomly assigned to condition at a 1:1 ratio. Randomization will be stratified by child medication status (on or off ADHD medication at the time of consent) and practice site (seven practices).

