## A priori plans for data analysis for each objective

### Objective 1 (Evaluate differences between PASS and TAU in improving service utilization and child health outcomes)

To evaluate changes in service utilization, we will examine between-group changes in the proportion of children receiving mental health services (i.e., outpatient mental health therapy, school mental health services and special education services, and psychotropic medication) from pre-treatment to post-treatment to follow-up using the McNemar test. To evaluate the effect of intervention on child outcomes, a mixed effects model with repeated measures (MMRM) will be the general analytical approach employed. The model will examine intervention effects across four time points (baseline, mid-treatment [parent report of homework performance and behavior compliance only], post-treatment, follow-up). Data for all participants randomized to treatment condition will be included in the analytic model, consistent with an intent-to-treat (ITT) approach. Mixed effects models will estimate within-subject effects by time and between-treatment effects, as well as the interaction of time by treatment. A significant time by treatment interaction will indicate that one treatment is superior to the other. MMRM will include the fixed categorical effects of treatment, time, randomization stratification factor (medication status and primary care practice), and treatment-by-time interaction as well as covariates as indicated. Within-participant error variance–covariance will be assumed to be an unstructured matrix. Point estimates and confidence intervals for the mean change in outcomes for each treatment group as well as the difference in the estimated mean change between groups will be calculated.

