Most of the outcome domains examined under Objective 1 include two measures. For example, there are two primary outcome measures – parent report of homework problems and parent report of behavior problems. In addition, ADHD symptoms will be assessed by parent report of inattention and hyperactivity-impulsivity symptoms. Because each domain generally will be assessed using two measures, tests of significance within each outcome domain will be examined using an adjusted *p* value. We have elected to use the conservative Bonferroni approach, and therefore will use a p value of 0.05/2 = 0.025. As indicated, analyses of measures completed by teachers will be underpowered. We will conduct these analyses using a* p* value of 0.05, but the primary focus will be on evaluating the magnitude of the effect size.

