### Objective 2 (Evaluate differences between PASS and TAU in changing parenting practices, improving family empowerment in seeking services, and improving caregiver perceptions of team-based care)

MMRM using an ITT approach will be the general analytical approach for testing Objective 2. The analytic model for examining Objective 2 will examine intervention effects across three time points (baseline, post-treatment, follow-up). We will test for significance using a *p* value of 0.025 to be consistent across analyses.

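### The stated 85% power for 0.30 SD does not fit the planned treatment-by-time test; with the protocol's own inputs that test has roughly 18–57% power, and about 39% for a single-visit change contrast

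*Protocol article*

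**What the plan says.** The Sample size section gives the planning inputs: "Projecting an enrollment of 300 participants (150 per condition), and given an expected 20% attrition rate, we expect 240 participants" with baseline and at least one later assessment, and "we assumed a standard deviation for a single observation = 0.50 and an autocorrelation = 0.3". It expects effects of 0.35 to 0.60 SD and concludes that "analytic models will achieve 85% power to detect an effect size as small as 0.30 SD". It ties this figure to the statistical methods that follow in the article, but names no contrast, significance level, number of visits or covariance pattern.

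The methods that follow are in the Objective 1 analysis section. The mixed model for repeated measures has baseline as one of its response time points: "The model will examine intervention effects across four time points", the mid-treatment one applying only to the two primary parent-report measures. The decision rule is: "A significant time by treatment interaction will indicate that one treatment is superior to the other". The estimate to be reported is the between-group difference in mean change. For outcome domains with two measures, the authors "therefore will use a p value of 0.05/2 = 0.025". Objective 2 uses the same type of model with three time points and the same level. The section on intervention effect sizes defines the effect as the difference in change divided by the unadjusted baseline SD.

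**The concern.** Low correlation between visits has opposite effects on two kinds of test. It helps a group difference averaged over visits, because nearly independent visits average out noise. It hurts a change-from-baseline contrast, because the baseline then adds noise instead of removing it. With a correlation of 0.3, a change score has a larger variance than a single observation. A claim of 85% power for 0.30 SD with 120 per arm is therefore surprising for a test of change.

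If the figure belongs to a different test from the one that decides superiority, the article credits the trial with a sensitivity that its analysis does not have. Readers who judge a null result by the planning statement could then take an effect of 0.30 SD to be unlikely when the trial had less than an even chance of detecting it.

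**Working it through.** **Inputs.** n = 120 per arm (240 evaluable from Sample size; "Participants will be randomly assigned to condition at a 1:1 ratio"). Effect d = 0.30 in single-observation SDs, so the SD of 0.50 cancels (0.30 SD is 0.15 raw units). Correlation ρ = 0.3. Level 0.025 from the Objective 1 analysis, with 0.05 as a check. Two-sidedness and complete data at the visits used are assumptions.

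**Formula.** Power = Φ(d/√(2v/n) − z), where v is the variance of the contrast in SD² and z = 2.241 (two-sided 0.025) or 1.960 (two-sided 0.05).

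**Step 1: what comes close to 85%.** Group difference averaged over three visits, 0.30 SD at each, level 0.025:
- Equal correlations: v = (3 + 6×0.3)/9 = 0.533. 0.30/√(2×0.533/120) = 3.18; Φ(3.18 − 2.24) = 83%.
- First-order autoregressive, AR(1): v = (3 + 2(0.3 + 0.3 + 0.09))/9 = 0.487. Φ(3.33 − 2.24) = 86%.

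This is a treatment effect averaged over time, not an interaction.

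**Step 2: change from baseline to one visit.** v = 2(1 − 0.3) = 1.40; standard error √(2×1.40/120) = 0.1528.
- 0.30 SD: 0.30/0.1528 = 1.964. Φ(1.964 − 2.241) = 39% at 0.025; Φ(1.964 − 1.960) = 50% at 0.05.
- 0.35 SD: 0.35/0.1528 = 2.291. Φ(2.291 − 2.241) = 52% at 0.025.
- Effect detectable with 85% power at 0.025: (2.241 + 1.036)×0.1528 = 0.50 SD.
- Evaluable per arm for 85% power at 0.30 SD: 2×1.40×(2.241 + 1.036)²/0.30² ≈ 335.
- If correlation decays as AR(1), the last-visit contrast has 30% (three time points, correlation 0.09) or 28% (four, correlation 0.027).

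**Step 3: average of post-baseline visits minus baseline, level 0.025.**

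| Time points | Covariance | v | Power |
|---|---|---|---|
| 3 | equal | 1 + 0.65 − 0.60 = 1.05 | 51% |
| 3 | AR(1) | 1 + 0.65 − 0.39 = 1.26 | 43% |
| 4 | equal | 1 + 0.533 − 0.60 = 0.933 | 57% |
| 4 | AR(1) | 1 + 0.487 − 0.278 = 1.209 | 45% |

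At 0.05 the highest of these is 67%.

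**Step 4: omnibus interaction, level 0.025.** Noncentral chi-square with 2 or 3 degrees of freedom and noncentrality δ′V⁻¹δ, where δ holds the differences in change and V their covariance matrix.

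| Effect pattern | Time points | Equal correlations | AR(1) |
|---|---|---|---|
| 0.30 SD at every post-baseline visit | 3 | 41% | 34% |
| same | 4 | 39% | 31% |
| rising in equal steps to 0.30 SD at the last visit | 3 | 30% | 23% |
| same | 4 | 28% | 18% |

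**Step 5: does another reading rescue the figure?** For the single-visit change contrast at two-sided 0.025:
- Retaining all 150 per arm: 48% (59% at 0.05).
- One-sided 0.025: 50%.
- Correlation needed for 85% power: about 0.75, against the stated 0.3.

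**Step 6: baseline-adjusted contrasts, level 0.025, 0.30 SD.** These belong to a different model from the one described.
- Single visit: v = 1 − 0.3² = 0.91; Φ(2.436 − 2.241) = 58%; 85% power at (2.241 + 1.036)×√(2×0.91/120) = 0.40 SD.
- Average of two post-baseline visits: v = 0.65 − 0.3² = 0.560 (equal) or 0.65 − 0.195² = 0.612 (AR(1)); 81% or 77%.
- Average of three post-baseline visits: v = 0.533 − 0.3² = 0.443 or 0.487 − 0.139² = 0.467; 89% or 88%.

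**The case against.** **The arithmetic may be sound.** A reader might infer a calculation error. The document does not support that: a visit-averaged group difference comes within about two points of 85%, so the figure may be correct for another test. Which test produced it cannot be known from the article, and a condensed article may leave the software settings to a fuller document. This stands, and the point is therefore a mismatch between two stated items. It is more than an omission, because the article itself links the figure to the methods that follow and then gives a decision rule that does not deliver it.

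**39% is one reading among several.** The protocol does not designate a one-degree-of-freedom contrast at 16 weeks as its primary test. It names an interaction over all time points and gives post-treatment and follow-up equal standing. This also stands, which is why ranges are given. All of them fall well short of 85%.

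**Baseline adjustment would help.** A reader might infer that 58% is the most that adjustment can achieve. It is not: that holds for one visit only, and averaging over three post-baseline visits, as the two primary outcomes allow, gives 88–89%. The data could thus support the claimed power under another analysis. But in the described model baseline is a response and the interaction decides, so this cannot be credited to the plan as written.

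**Consequences.** On the single-visit change contrast at 0.025, power is about 81% at 0.475 SD, the middle of the expected range, and 95% at 0.60 SD. The plan also commits to confidence intervals, and these, not the planning power, show what a null result excludes. Both points moderate the consequences without making the stated figure right.

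**Conclusion.** The stated power does not belong to the stated test. With 120 per arm and correlation 0.3, no two-sided form of the change or interaction test examined here reaches 85% for 0.30 SD, at 0.025 or at 0.05. At 0.025 power is about 39% for a single-visit change, 18–41% for the omnibus interaction and 43–57% for the average post-baseline change. The effect that a single-visit change contrast detects with 85% power is about 0.50 SD, inside the expected range but well above its lower end.

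These figures assume a two-sided test, effects in baseline-SD units, normal approximations and complete data at the visits used. The 240 need only one assessment after baseline, so fewer may be seen at any given visit.

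A reader might go further and infer that the trial is too small for its purpose. The documents do not support that: power is high towards the upper end of the expected range, and a baseline-adjusted analysis averaged over visits would come near or above the claimed figure.

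**What to change.** Enrolment need not change under either route.

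1. **Keep the model and correct the statement.** In Sample size, name the contrast, significance level, sidedness, visits and covariance pattern behind the power figure. Restate the power for the planned interaction or change test: about 39% for 0.30 SD and 85% for about 0.50 SD on a single-visit change contrast at 0.025, with the omnibus range if that test decides. The cost is a text edit and a less favourable figure.

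2. **Change the deciding contrast.** Before any unblinded analysis, prespecify a baseline-adjusted PASS versus TAU contrast and quote its own power at 0.025. For 0.30 SD this is about 58% at a single visit (85% for about 0.40 SD), 77–81% averaged over two post-baseline visits, or 88–89% averaged over three for the two primary outcomes. This alters the model and the decision rule in the Objective 1 analysis, so it needs an amendment. Averaging also answers a different question from the separate post-treatment and follow-up comparisons in the study objectives, and the text should say so.
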